**1a TITLE**

**Non-pharmacological Prevention of Postoperative Delirium by Occupational Therapy Teams: a randomized clinical trial**

**1b SUMMARY**

**Background:** It has been described that a quarter of all surgeries are performed on older adults, and that up to 50% of elderly patients may develop postoperative delirium (POD).[(1,2)](https://paperpile.com/c/YGPhmB/MaBdk+QfL5C) Patients with POD have worse short- and long-term clinical outcomes, such as increased postoperative morbidity, increased hospital stay, higher hospital costs, cognitive and functional impairment, and higher post-surgery mortality.^1–4^ In addition, it has been determined that delirium is preventable,^5^ and therefore, effective prevention measures should be established to generate benefits in the health of patients and reduce health costs. On the other hand, it has been seen that intervention with occupational therapy (OT) in non-mechanically ventilated elderly patients hospitalized in critically ill patient units, managed to significantly reduce the incidence and duration of delirium compared to a standard intervention.^6^ However, we do not know whether OT interventions can be effective in this population.

**General Objective**: To determine the efficacy of a non-pharmacological preventive intervention performed by occupational therapy teams in the incidence of postoperative delirium (POD) and POD subsyndromal (PODS) in patients older than 75 years undergoing highly complex elective surgeries.

**Design/Method:** Randomized clinical trial (RCT), multicenter, prospective, with parallel groups, in a 1:1 ratio, in 2 Chilean hospitals (Hospital Clínico Universidad de Chile (HCUCH) and in the Complejo Hospitalario San José (CHSJ)).

**Participants:** Patients aged 75 years or older, admitted to the hospital, who will undergo highly complex elective surgery at the HCUCH or CHSJ, and who have provided their consent, will be studied. Patients with known cognitive impairment prior to admission, severe communication disorder and cultural limitation of language, delirium upon admission or prior to the start of the intervention, and patients enrolled in another study will be excluded.

**Intervention:** A control group (standard non-pharmacological prevention of delirium measures) or an intervention group (early and intensive OT + standard non-pharmacological prevention of delirium measures) will be randomized. The intervention group will receive 2 daily sessions of 30 minutes, for 5 days, receiving a total of 10 OT sessions, which considers a predefined protocol of actions according to the patient's condition.

**Evaluations:** The presence of POD and PODS will be evaluated with the Confusion Assessment Method (CAM), mortality, functional independence, and motor and cognitive state at discharge. In addition, sociodemographic and clinical data will be included.

**2a INTRODUCTION**

Around the world, 230 million surgeries are performed per year and a third of the patients who undergo surgeries are over 65 years old.[(3,4)](https://paperpile.com/c/YGPhmB/wYG4j+a74uw) Worryingly, depending on the complexity of the surgery, between 10 and 70% of elderly patients develop POD.[(1,2)](https://paperpile.com/c/YGPhmB/MaBdk+QfL5C) These patients with POD have poor short- and long-term clinical outcomes, such as an increase in postoperative morbidity, a prolonged hospital stay, a deterioration in functional and cognitive status, and even an increase in mortality one year after surgery.[(1,2,5,6)](https://paperpile.com/c/YGPhmB/MaBdk+QfL5C+UrXRC+ipt2K) Consequently, these poor results are associated with a poorer quality of life of the elderly and an increase in health costs. Delirium has been determined to be preventable through various non-pharmacological interventions,[(7,8)](https://paperpile.com/c/YGPhmB/XLxQg+FZcGe) which constitute the first-line preventive tools, and which have the best clinical results. Consequently, they reduce the costs of health care for the elderly. However, both prevention and diagnosis of POD are still deficient in routine clinical practice worldwide and in our country. Therefore, it is essential to create protocols and recommendations that not only allow the prevention of POD but are also applicable in the health centers that serve the elderly adults who will undergo various surgeries.

POD is the delirium that occurs after surgery and is defined by the DSM-5 as an acute and fluctuating disorder, characterized by an altered state of consciousness, loss of attention and disorganized thinking.[(9)](https://paperpile.com/c/YGPhmB/9XO7q) This condition occurs during the first week after surgery and lasts an average of 3 days.

***POD Risk factors and triggers***

It is accepted that POD is the result of the interaction of risk factors and triggering factors, which ultimately alter brain function, causing acute cognitive impairment.[(10,11)](https://paperpile.com/c/YGPhmB/Bws4y+aUNwV) The risk factors of patients associated with POD are: older age, less schooling, malnutrition, a higher rate of comorbidity, a history of alcohol abuse and having a cognitive alteration prior to surgery.[(6,12)](https://paperpile.com/c/YGPhmB/ipt2K+EBNPA) Regarding surgical injury, if it is on a larger scale, the possibility of developing POD increases since the systemic inflammatory response is more intense and blood losses are more abundant, causing a decrease in cerebral perfusion.[(11)](https://paperpile.com/c/YGPhmB/aUNwV) The types of surgeries that have a greater association with POD are cardiac surgeries (46-70%),[(5,13)](https://paperpile.com/c/YGPhmB/UrXRC+OsXIE) major abdominal surgeries (18-24%)[(14,15)](https://paperpile.com/c/YGPhmB/v0D4a+uVprT) and hip replacement surgeries (3.6-53-3%).[(4,16)](https://paperpile.com/c/YGPhmB/a74uw+RgLNq) Finally, some drugs used in anesthesia increase the risk of developing POD, such as anticholinergics (atropine), benzodiazepines, opioid derivatives (morphine, fentanyl and tramadol),[(10,17)](https://paperpile.com/c/YGPhmB/Bws4y+IUAbX) in addition to the hypnotic depth evaluated by BIS,[(18)](https://paperpile.com/c/YGPhmB/z1x6g) among others. In short, these factors work together to alter brain function, which underlies the development of POD.

Therefore, when faced with a risk patient who will undergo major surgery, preventive measures can be taken to reduce the development of POD, such as avoiding the use of certain drugs, maintaining adequate cerebral perfusion, and reducing systemic inflammation.

***Prevention of POD***

As mentioned at the beginning, the cost-benefit balance is higher with prevention measures than with therapeutic measures. Therefore, the focus of this proposal is the prevention of POD to implement the results in different public and private health centers in our country. Next, we will detail the recommended measures to prevent POD.^20^

- **Preoperative:** The use of certain drugs, such as benzodiazepines, anticholinergics should be avoided, decrease the fast times, maintain the circadian day-night rhythm and the use of sedative drugs such as α2-agonists (dexmedetomidine or clonidine) should be considered.[(17,19)](https://paperpile.com/c/YGPhmB/Ty2Dk+IUAbX) In addition, the risk of each patient must be adequately stratified in relation to the presence of predisposing factors and the surgery to which they will undergo.
- **Intraoperative:** At this stage, the approach is to diagnose and treat any complications that may occur early. In addition, the use of benzodiazepines and atropine in anesthetic management should be avoided, and nociception during surgery should be properly managed using techniques that reduce the use of opioid derivatives such as the use of regional anesthesia techniques. Finally, it is recommended to monitor the anesthetic depth to avoid very deep anesthesia.[(19,20)](https://paperpile.com/c/YGPhmB/Ty2Dk+TkOzl)
- **Postoperative:** After surgery, all patients should undergo non-pharmacological measures to prevent POD. These measures consist of stimulating patient orientation with the use of watches and communication; facilitate the early use of glasses and hearing aids; reduce ambient noise and facilitate patients' sleep; avoid the use of unnecessary intravenous and urinary catheters; stimulate mobilization and early feeding; and use multimodal analgesic techniques in order to reduce opioid doses.[(8,19)](https://paperpile.com/c/YGPhmB/FZcGe+Ty2Dk) In conjunction with the above, the POD should be investigated early, even from the post-anesthesia recovery unit.[(19)](https://paperpile.com/c/YGPhmB/Ty2Dk)

Regardless of the perioperative stage in which the prevention of POD is carried out, measures with a non-pharmacological approach and others that require the use of drugs can be described. It is noteworthy that non-pharmacological measures are less expensive, are more applicable in health systems, and there is evidence that they are effective in reducing POD rates.[(8,21)](https://paperpile.com/c/YGPhmB/FZcGe+p4TfB) In our vision as a group, which is supported by the literature, we believe that the measures with more evidence and a better cost-effectiveness profile are non-pharmacological preventive measures. For this reason, this proposal focuses on this type of measures covering the perioperative.

***Previous work of the research team on prevention of delirium.***

Part of the research team studied whether the intervention by OT prevents the development of delirium in elderly adults hospitalized in critical patient units.[(22)](https://paperpile.com/c/YGPhmB/b8oXl) This study was carried out at the HCUCH and enrolled a total of 140 hospitalized patients in the Critical Patient Unit without the need for mechanical ventilation. They were subdivided into 2 groups, the control group underwent standard non-pharmacological prevention measures for delirium, that is: time and space orientation measures, stimulation of early mobilization, correction of sensory deficits, establishment of a more welcoming environment with caregivers avoiding the use of physical limiting measures, sleep protection and avoiding the use of delirium-promoting drugs. The experimental group underwent the same standard protocol plus early and intensive OT, which consisted of polysensory stimulation, improving the positioning of the patient in bed, cognitive stimulation, motivation in performing the basic activities of daily life, stimulation of the activity of the upper extremities and fostering family participation. Interestingly, the rate of delirium decreased significantly from 20% in the control group to 3% in the treatment group, which in turn led to a decrease in the days with delirium and patients had better functionality at discharge. These results indicate that the measures carried out by OT are highly effective and suggest that in the perioperative context they could be very effective in preventing the development of POD in elderly patients.[(22)](https://paperpile.com/c/YGPhmB/b8oXl)

***Final considerations***

Every day, in all the hospital centers of the country, elderly adults undergo all kinds of surgeries and what is required is that they regain their functionality as soon as possible. The multidisciplinary team in this scenario is critical and rehabilitation must be early and intensive, on a functional and cognitive level since these are the critical elements for an adequate recovery. Our research group has determined that the interventional work of OT is essential in the prevention of cognitive impairment in patients in the Critical Patient Unit. Therefore, it is relevant and necessary to study whether this therapy is effective in the perioperative period to prevent the development of POD.

**2b HYPOTHESIS AND OBJECTIVES**

The present study hypothesizes that the non-pharmacological prevention of postoperative delirium carried out by occupational therapy teams decreases the incidence rate of delirium compared to standard prevention therapy in patients older than 75 years of age undergoing highly complex elective surgeries.

The primary objective of the study is to determine the efficacy of a non-pharmacological preventive intervention performed by occupational therapy teams in the incidence of postoperative delirium and subsyndromal postoperative delirium in patients over 75 years of age who underwent highly complex elective surgeries.

Specific objectives include:

- To characterize adults over 75 years of age who underwent highly complex elective surgeries during the first 5 postoperative days.
- To evaluate the impact of non-pharmacological preventive intervention carried out by occupational therapy teams or standard prevention on the duration of delirium and hospital stay in patients over 75 years of age subjected to highly complex elective surgeries.
- To evaluate the impact of non-pharmacological prevention on the functionality of patients over 75 years of age undergoing highly complex elective surgeries.

**3 METHODS AND PROCEDURES**

**3a TRIAL DESIGN**

A randomized clinical trial (RCT) is proposed with a multicenter prospective, with parallel groups, in a 1:1 ratio, in 2 Chilean hospitals. The records will be made at the beginning of the study, during the interventions, and at hospital discharge.

For RCT planning, the CONSORT[(23)](https://paperpile.com/c/YGPhmB/4F2IU) methodological recommendations for reporting non-pharmacological trials are used, in addition to the TIDieR[(24)](https://paperpile.com/c/YGPhmB/ZcWDA) and SPIRIT standards.[(25)](https://paperpile.com/c/YGPhmB/FtlaA)

**3b PARTICIPANTS**

Patients older than 75 years of age, who must have a highly complex elective surgery at the HCUCH or CHSJ. The criteria are described in Table 1

**Table 1. Admission criteria**

| **Inclusion Criteria** | **Exclusion Criteria** |
| --- | --- |
| - Age equal to or greater than 75 years - Hospital admission for highly complex elective surgery - Consent by patient | - Known cognitive impairment prior to admission. Mini-Mental State Examination (MMSE) with <23 points in case the subject has 6 or more years of schooling and <18 points in case the subject has <6 years of schooling. - Severe communication disorder and cultural limitation of language (language other than Spanish) - Delirium at admission or prior to the start of the intervention (measured with CAM) - Patient enrolled in another study |

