**Interventional group – Early and intensive Occupational Therapy**

Regarding OT intervention, specific training must also be carried out for the group of occupational therapists, to properly implement the OTs´ own strategies.

The OT intervention is implemented for 5 consecutive days, 2 times a day, in sessions before noon, and sessions after noon, and each session lasts 30 minutes.

The interventions to be carried out are grouped into the following 6 prevention areas (Table 3):

1. **Polysensory stimulation**: consisting of providing the patient with intense external stimulation regulated by different sensory channels (visual, auditory, tactile, proprioceptive and gustatory), with the objectives of increasing alertness, preventing sensory deprivation and increasing interaction of the patient with the objects and people around him/her (GES-ACV 2013 Clinical Guide recommendation).[(26)](https://paperpile.com/c/YGPhmB/mZ0v7) Sensory stimulation protocols have proven to be effective in other pathologies, such as states of minimal consciousness and dementia.[(27)](https://paperpile.com/c/YGPhmB/zBbzD) States that share some elements with delirium, therefore, can be used in patients with POD.
2. **Positioning:** consists of the early installation of orthosis and adaptations that leave areas with the highest frequency of bedsores free of pressure (sacral region, heels, among others). Proper positioning of the patient makes it possible to reduce the appearance of joint stiffness, which generates a positive impact on the patient's functionality in activities of daily living and, therefore, a reduction in the burden for health providers and their family.[(28)](https://paperpile.com/c/YGPhmB/cxK4s) They also reduce the appearance of pressure ulcers, one of the conditions that causes longer hospital stays and higher costs, and finally, it allows to provide comfort to the patient during hospitalization.
3. **Cognitive stimulation**: intervention aimed at keeping mental functions active. According to the International Classification of Functionality these are: consciousness, orientation, attention, memory, calculation, praxis and language, which are included in 6 areas of action: i) attention and wakefulness, ii) visual perception, iii) memory, iv) calculation and problem solving, v) praxis and vi) language.[(22)](https://paperpile.com/c/YGPhmB/b8oXl)

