**9 ALLOCATION CONCEALMENT MECHANISM**

This will be done by a researcher, who will carry out the registration and randomization process, saving the information on his/her personal computer.

It should be remembered that all patients, once recruited, will begin to receive care as per the standard non-pharmacological prevention of delirium measures measures.

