**10 IMPLEMENTATION**

Recruitment will be carried out by one professional responsible for the health team of each center, who will identify and recruit potential patients. Once consent is obtained, they will inform the person in charge of randomization (independent statistician) via telephone message. The person in charge of randomization will notify the coordinator of each center which group the patient was assigned to, which may be a control or interventional group, starting the implementation of the study.

The coordinator of each center that carries out this process will not have contact with the evaluators, auditors, and the person responsible for the data analysis.

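### The delirium exclusion runs to the start of the intervention instead of randomisation, so a randomised patient can be excluded for what may be a primary-outcome event

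*Protocol*

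**What the plan says.** Table 1 of the protocol lists as an exclusion "Delirium at admission or prior to the start of the intervention (measured with CAM"). The participants paragraph of the summary has the same rule: "delirium upon admission or prior to the start of the intervention". Admission and the start of the intervention are separate limbs, so the second must cover time after admission.

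Section 10 gives the order of events. "Once consent is obtained, they will inform the person in charge of randomization (independent statistician) via telephone message". Then "The person in charge of randomization will notify the coordinator of each center which group the patient was assigned to", and implementation begins. Section 9 adds that "all patients, once recruited, will begin to receive care as per the standard non-pharmacological prevention of delirium" measures, in either arm.

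For OT, section 4 gives frequency and length only: "The OT intervention is implemented for 5 consecutive days, 2 times a day". No start day is given relative to randomisation or surgery. The primary objective in section 2b uses the word intervention for the OT programme: "a non-pharmacological preventive intervention performed by occupational therapy teams".

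**The concern.** Eligibility should close no later than randomisation. Here the stated cut-off can fall after it. A CAM-positive result in between meets an exclusion criterion and may also meet the primary outcome definition, and the protocol does not say which prevails.

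The cut-off also has a natural meaning in the OT arm (the first session) but no clear one in the control arm, which has no OT session and whose standard measures have been running since recruitment. If sites applied the rule literally on that reading, early cases could leave the OT arm while the same cases in control counted as events. That would be an exclusion after randomisation that depends on both outcome and arm, and it would lower the observed rate under OT even if OT did nothing.

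**Working it through.** **Step 1: order of events.**

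| Event | Where | Timing given |
|---|---|---|
| Consent, then randomisation | Section 10 | Randomiser informed once consent is obtained |
| Arm told to the centre coordinator | Section 10 | Before implementation |
| Standard measures, both arms | Section 9 | From recruitment |
| First OT session | Section 4 | Not dated |
| Exclusion closes | Table 1, summary | Start of the intervention |

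Allocation must precede the first OT session. The length of the gap is unknown.

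**Step 2: overlap with the outcome.** The protocol gives three outcome windows: the first five days in hospital (section 5, assessment of the primary outcome), the first five days after surgery or to discharge if sooner (section 6), and any time after surgery (section 12). None is stated to begin at the first OT session, so a positive CAM before that session may fall inside the window.

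**Step 3: the planned sample size.** Inputs from section 6: 20% against 5%, 80% power, two-sided 0.05, 10% loss, 80 per group.
- Unpooled normal approximation: 73 per group; 73 / 0.90 = 81.1, so 82.
- Arcsine approximation: 70 per group; 70 / 0.90 = 77.8, so 78.
- Pooled-variance formula: 76 per group, 85 after inflation.

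The stated 80 lies between the first two. This point does not change it.

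**Step 4: illustration of size.** Assumptions: no true effect; p = 20% delirium in both arms; 80 randomised per arm; a share q of cases arises between randomisation and the first OT session; these are removed from numerator and denominator in the OT arm only. The protocol does not give q.

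Observed OT rate = p(1 − q) / (1 − pq). Patients removed = 80pq.

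The test is a pooled z-test. With d the difference in rates, SE0 the pooled and SE1 the unpooled standard error, rejection = Φ((d − 1.96·SE0)/SE1) + Φ((−d − 1.96·SE0)/SE1).

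For q = 25%:
- Removed: 80 × 0.20 × 0.25 = 4, leaving 76 in the OT arm.
- OT rate: 0.15 / 0.95 = 15.8%, so d = 4.2 points.
- Pooled rate: (16 + 12) / 156 = 0.179; SE0 = 0.0615, SE1 = 0.0612.
- Rejection: Φ(−1.28) + Φ(−2.66) = 0.100 + 0.004 = 0.104.

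| q (assumed) | Removed from OT arm | Observed OT rate | False difference | Two-sided type I error |
|---|---|---|---|---|
| 0 | 0 | 20.0% | 0 points | 0.050 |
| 10% | 1.6 | 18.4% | 1.6 points | 0.058 |
| 25% | 4.0 | 15.8% | 4.2 points | 0.104 |
| 50% | 8.0 | 11.1% | 8.9 points | 0.320 |

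A simulation of 200,000 runs gave 0.050, 0.058, 0.105 and 0.323. With the 21% historical rate from section 6, the false differences for q of 10%, 25% and 50% are 1.7, 4.4 and 9.3 points.

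**Step 5: after the change.** With the cut-off at randomisation and events counted from the same point in both arms, nobody is removed, the artefact is 0 points and type I error stays at 0.05.

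**The case against.** The strongest reply is that no passage orders the removal of a randomised patient, from one arm or from both. Table 1 is headed as admission criteria, and the summary lists the item among screening conditions, so an eligibility check before randomisation is a possible reading. This stands: one-sided exclusion is permitted by the wording and not prescribed by it.

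Second, intervention need not mean OT. The summary's intervention paragraph and section 4 cover both programmes, section 7 lists standard measures and OT together as interventions, and section 8B says all patients receive prevention interventions. On that reading the cut-off is the start of study care, which section 9 places at recruitment in both arms, and there is no asymmetry. This also stands as a possibility. Section 2b points the other way, and nothing decides between them.

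Third, the gap is undated. Section 10 suggests that implementation follows allocation directly. If the five days of CAM in section 5 ran alongside the five days of OT, a positive result before the first session would fall outside the outcome window. The gap may therefore be short and the overlap nil, but the other outcome windows do not secure this.

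Fourth, section 11 blinds evaluators and the analyst, and section 10 keeps the coordinator away from them. That protects the CAM rating. It does not govern who decides to exclude a patient, and the coordinator and treating therapists know the arm.

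Fifth, the handling of ineligible randomised patients is often left to an analysis plan, which is not at hand. That is true of analysis sets, but eligibility and its time anchor belong in the protocol.

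A reader might also infer that events in the gap are sure to be found, because the introduction recommends looking for delirium from the recovery unit. That remark is background, not a trial procedure, and gives no support here.

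**Conclusion.** The point holds as a bias risk that the wording permits. The exclusion is not tied to randomisation, no other passage closes eligibility there, and the same CAM result may be both a reason for exclusion and a primary event.

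A reader might go further and infer that the plan drops early delirium from the OT arm and counts it in control, with type I error well above 5%. The protocol does not support that. It does not say that randomised patients are dropped from one arm, it leaves the meaning of intervention open, and it gives no interval from which the early share could be derived. The range from 0 to 8.9 points and from 5% to about 32% is conditional on an assumed early share of 0 to 50%, no true effect, 20% delirium, 80 per arm and removal from the OT arm only. If the early share is zero or the cut-off is symmetric, this arm-dependent bias does not arise. Against the planned difference of 15 points, four patients removed (the 25% case) would produce 4.2 points, so the ambiguity deserves correction although its size is unknown.

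**What to change.** - In Table 1 and the summary, change the exclusion to delirium (CAM-positive) at any time before randomisation.
- State that every randomised patient stays in the assigned arm, whether or not an OT session has been given.
- Count CAM-positive evaluations from one time point, defined identically in both arms and not tied to the first OT session. Reconcile the outcome windows in sections 5, 6 and 12 with it.

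The cost is a short amendment to the eligibility wording plus the reconciliation of the windows. The planned 80 per group is unchanged. The downside is that some events before any OT exposure will count in the OT arm, so the observed effect may be slightly smaller. If eligibility was always meant to close at randomisation, the change to the exclusion only makes that explicit.
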